### **Data collection: first questionnaire (see attachment B)**

The first questionnaire consists of several parts. All questions have been developed for this study, based on the questionnaire of our previous intervention study, unless otherwise indicated.

- Questions to measure patients' knowledge about residual tissue use. These questions have been developed for this study.
- Questions about how patients perceived the information about residual tissue use (both brochures and verbal information) they received, and how they would have liked to be informed.
- Questions to assess whether patients were aware of the fact that they could have had an influence on residual tissue use and if so, which decision they made.
- Questions to assess patients' satisfaction with the consent procedure and their preferences for a consent procedure.
- Questions about what types of research patients want to give consent for (commercial research, different types of diseases, research in other hospitals), and how often they want to give consent (once or for each new protocol).
- Questions to assess feelings of ownership of the tissue, trust in research or the hospital, and how important they feel scientific research is. Some of these questions were developed by the Rathenau Institute.
- Questions to assess whether patients want feedback on unexpected findings in their residual tissue and whether not receiving feedback would influence their decision about residual tissue use.
- Questions about previous experiences with scientific research and tissue removal. Some of these questions were developed by the Rathenau Institute.
- Questions about demographics.
- Two subscales of the SF-12 to assess physical functioning and mental health.
- The PSQ-18, or Patient Satisfaction Questionnaire 18 will be used to assess patient satisfaction with medical care. The questionnaire has been developed based on a larger questionnaire, the PSQ-III. The original, English version of the PSQ-18 has been validated and demonstrated to be reliable (<http://www.rand.org/content/dam/rand/pubs/papers/2006/P7865.pdf>). Further, the Dutch version of the PSQ-III (Patienten Tevredenheidsvragenlijst) has been validated and demonstrated to be reliable. In this study, we will use three subscales of this scale, namely general satisfaction, interpersonal manner, and communication. Each subscale consists of two items.
- The Threatening Medical Situations Inventory (TMSI) to assess two ways in which people can cope with medical threat: monitoring, or cognitive confrontation, and blunting, or cognitive avoidance. Generally patients with a monitoring style tend to cope with (medical) stress by seeking information, while those with a blunting style cope by avoiding information. The questionnaire consists of four scenarios of medical

threat situations, followed by three monitoring and three blunting items that need to be answered on a five-point scale. The TMSI has been validated and demonstrated to be reliable in several groups of people, both patients and non-patients.

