### **Methods**

In this multicentre, randomized controlled trial, 1800 patients will be recruited from four hospitals in the Netherlands (expected response rate 75%). Patients will be randomized to three study arms. In the ‘informed consent’ and ‘opt-out plus’ arms, patients are informed about residual tissue use both verbally and through a specific leaflet. These leaflets contain a consent form and an opt-out form respectively. In the third arm, the control group, no (extra) information about residual tissue use is offered, and patients may opt-out of the use of their residual tissue verbally or written. Patients to be included will be stratified by hospital and condition. Two academic and two regional hospitals will be included. Inclusion of both categories of hospitals and of patients with malignant and non-malignant diseases will increase the generalizability of the study results.

Six weeks after the intervention, patients will receive a questionnaire addressing satisfaction with and preference for the consent procedures. One quarter of the respondents will be interviewed about these topics through a semi-structured telephone interview. Six months after the intervention, respondents will receive a second questionnaire to examine whether those who made a decision about the use of their residual tissue are still aware of that decision and, if they are, whether they are still satisfied with it.

Clinicians and nurses who will carry out the interventions will receive a pre- and post-experimental questionnaire to examine their opinions about and experiences with the consent procedures.

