## **Study objectives**

The main part of this study aims to determine patient preferences for and satisfaction with consent procedures regarding the use of residual tissue for research, to provide insight into the type of information patients need to decide on the use of their material in research, and to determine the optimality of the timing and the content of these procedures in clinical practice. We will compare the three consent procedures, opt-out, opt-out plus and informed consent, with respect to the following primary study outcomes:

1. Patients' satisfaction with and preference for a consent procedure
2. Proportion of patients aware of storage of tissue and research use
3. Consent rates
4. Medical staff's satisfaction with and preference for a consent procedure

Additionally, we will obtain information on (1) the proportion of non-consent due to non-response; (2) the characteristics of non-consenters and non-respondents; and (3) the reasons for providing or withholding consent or (non-)response. We will investigate how patients perceived the information they received about residual tissue use and their knowledge about this topic. Patients' preferences to provide or withhold consent for specific types of research (e.g. genetic, commercial) and feedback regarding unanticipated findings will be investigated as well. Further, we will examine whether consent rates, satisfaction with or preference for a consent procedure differ according to severity of disease, type of clinical procedure (e.g., biopsies or surgical removal of tissue), diagnosis, type of hospital (academic or community) or demographics. Six months after the first questionnaire, we will examine whether patients are still aware of the decision they made and whether they are still satisfied with their choice to provide or withhold consent.

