## **Hypotheses**

Hypotheses regarding the primary study outcomes are:

1. Patients' will be significantly more satisfied with the informed consent and opt-out plus consent procedures than with the opt-out consent procedure
2. Most patients will prefer the opt-out plus consent procedure, the lowest proportion of patients will prefer the opt-out consent procedure.
3. Significantly more patients will be aware of storage of tissue and research use in the informed consent and opt-out plus procedures than in the opt-out procedures.
4. Consent rates will be highest in opt-out and opt-out plus.
5. Members of the medical staff will be most satisfied with and prefer the opt-out and opt-out plus procedures.

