## **Outcomes**

The primary study outcomes will be used to determine which consent procedure serves the needs of patients, clinicians and scientific research best. If one of the three consent procedures serves the needs of all three of these parties best, we will conclude that this consent procedure is the best candidate to become the standard procedure in the Netherlands that prescribes whether and how patients should be asked consent for the use of residual tissue. If the needs of these three parties are best served by different consent procedures, or if it is unclear which consent procedure serves the needs of one or more of the parties best, we will organize an invitational conference in which we invite different stakeholders, such as clinicians, patient organizations and researchers, to discuss how to translate our research findings into clinical practice.

Which consent procedure serves a party's needs best will be decided along the following lines:

- For patients: satisfaction with the received information in the 'best procedure' should be significantly higher than in the consent procedure with the lowest satisfaction rates. Further, the consent procedure should have the highest preference rates among respondents, with a minimum of a 10% difference with the consent procedure with the lowest preference rate. Additionally, the proportion of patients aware of storage of tissue and research use should be at least as high as in the other two groups.

- For clinicians: satisfaction with the received information in the ‘best procedure’ should be significantly higher than in the consent procedure with the lowest satisfaction rates. Further, the consent procedure should have the highest preference rates among participating clinicians and nurse practitioners, with a minimum of a 10% difference with the consent procedure with the lowest preference rate. Additionally, more than 75% of the responding medical staff should indicate that the consent procedure ‘never’ or ‘seldom’ interferes with giving clinical information.
- For research: consent rates for the procedure for which patients and/or clinicians have the highest preference should be at least as high as consent rates in the two other procedures.

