After the intervention, we will include an informed consent form in the first questionnaire. With this form, we ask consent for the first and second questionnaire (see below). At the end of the questionnaire permission will be asked for a telephone interview.

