## ***List of attachments***

- A: Detailed information on the background of this study and on previous research
- B: First questionnaire
- C: Second questionnaire
- D: Pre-intervention questionnaire medical staff
- E: Post-intervention questionnaire medical staff
- F: Brochure opt-out plus intervention arm
- G: Brochure informed consent intervention arm
- H: Information leaflet Tissue Issue
- I: Consent form Tissue Issue
- J: Patient letter 1
- K: Patient letter 2
- L: Patient reminder 1
- M: Patient reminder 2
- N: Inserted sheet with pictures of brochures
- O: Checklist medical staff informed consent
- P: Checklist medical staff opt-out plus
- Q: Checklist medical staff opt-out

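### The awareness item named for questionnaire 1 does not match primary outcome 2 and is not protected from prompting by the mailing, and no date fixes consent status before that mailing

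*Protocol*

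**What the plan says.** **Outcome.** Study objectives lists as the second primary outcome "Proportion of patients aware of storage of tissue and research use". Hypotheses expects "Significantly more patients will be aware of storage of tissue and research use in the informed consent and opt-out plus procedures" than under opt-out. For the procedure judged best for patients, Outcomes requires that "the proportion of patients aware of storage of tissue and research use should be at least as high as in the other two groups". For research, the preferred procedure's consent rate must be no lower than the other two. Neither rule has a margin.

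**Measurement.** The first-questionnaire section names one awareness part: "Questions to assess whether patients were aware of the fact that they could have had an influence on residual tissue use". A separate part is "Questions to measure patients' knowledge about residual tissue use", whose content is not described.

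**Who is mailed, and when.** For controls, the summary says "no (extra) information about residual tissue use is offered". The intervention section adds that they may read the hospital's general leaflet. Questionnaires and interview has every recruited patient mailed at six weeks, counted from the intervention in the active arms and from surgery in controls. Non-respondents get a written reminder after a month and then a telephone reminder. On study consent: "After the intervention, we will include an informed consent form in the first questionnaire". That form covers the questionnaires, not tissue use. The attachments include a study leaflet, patient letters and "Inserted sheet with pictures of brochures".

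**Consent status.** Active-arm patients return a form by post, and controls may opt out orally or in writing. No closing date is given. The sample-size section plans 0.1% non-consent under opt-out plus or opt-out and 10% under informed consent.

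**The concern.** Two things are left open where the data are collected.

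First, the primary awareness outcome has no named item. Knowing that tissue is kept and used is not the same as knowing that one can object. A patient may know the first without the second, so the influence item would count that patient as unaware. If the outcome is taken from the knowledge block instead, nothing says the answer refers to what the patient knew before the envelope arrived. For controls the questionnaire may be the first specific notice that residual tissue is used in research and that they have a say. An analysis cannot later recover what they knew beforehand.

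Second, consent status stays open while the mailing and two reminders go out. Controls may opt out because of the questionnaire, and informed consent patients may be reminded to send an overdue form. Such changes would count as results of the consent procedure although the study's own measurement produced them. With decision rules that allow no margin, small changes can alter which procedure qualifies.

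**Working it through.** **1. The plan's own figure.** Inputs from the sample-size section: 0.1% versus 10% non-consent, 80% power, two-sided alpha 0.05, continuity correction, 121 per group.

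n = [1.96·√(2p̄(1−p̄)) + 0.842·√(p₁(1−p₁)+p₂(1−p₂))]² / d², then n′ = (n/4)·[1+√(1+4/(nd))]².

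With p̄ = 0.0505 and d = 0.099, n = 76 and n′ = 95, so the stated 121 does not reproduce. The same formula gives 121 for 1% versus 10%. That mismatch is a separate matter and the argument here does not depend on it.

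**2. Awareness.** The protocol gives no expected rates, so all rates here are assumed. If a share c of truly unaware patients report awareness because of the mailing, observed awareness is p + c(1−p). If c is equal in both arms, the difference shrinks by the factor (1−c). Power is at 450 per group, normal approximation with continuity correction.

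- True 80% versus 40% (40 points), equal c: c = 25% leaves 40 × 0.75 = 30 points, and c = 50% leaves 20. Power stays near 100%.
- The same rates, controls only: c = 25% gives 40 + 0.25 × 60 = 55%, leaving 25 points (power near 100%). c = 50% gives 70%, leaving 10 points (power about 93%).
- True 70% versus 60%, controls only, c = 10%: 60 + 0.10 × 40 = 64%, leaving 6 of 10 points. Power falls from 87% to 45%.

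The informed consent versus opt-out plus awareness contrast need not change, since both arms were informed beforehand.

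**3. Consent, informed consent versus opt-out.** The first row uses the planned rates and the rest are assumed. The 4.6% is the share in the earlier intervention study who would withhold consent or were unsure when asked by questionnaire, used here as an illustrative upper end. The 7.5% assumes a quarter of the planned 10% is forms that arrive late as consents (10 × 0.75).

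| Control non-consent | Informed consent non-consent | Difference (points) | n per group for 80% | Power at 121 | Power at 450 |
|---|---|---|---|---|---|
| 0.1% | 10% | 9.9 | 95 | 90% | >99% |
| 1% | 10% | 9.0 | 121 | 80% | >99% |
| 2% | 10% | 8.0 | 162 | 65% | >99% |
| 4.6% | 10% | 5.4 | 400 | 28% | 85% |
| 0.1% | 7.5% | 7.4 | 130 | 77% | >99% |
| 2% | 7.5% | 5.5 | 269 | 40% | 96% |
| 4.6% | 7.5% | 2.9 | 1128 | 10% | 39% |

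The 121 column matters because the plan counts on subgroups of 90 to 150.

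**4. Consent, opt-out plus versus opt-out.** Both are planned at 0.1%. With 600 per arm that is 600 × 0.001 = 0.6 expected non-consenters. One extra opt-out moves an arm's rate by 1/600 = 0.17 points, more than the whole planned rate. A few mailing-prompted opt-outs can therefore set the order of the two arms.

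**The case against.** The strongest reply is that much of this depends on attachments that are not shown, and several stronger readings do fail.

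- *Awareness is asked after the knowledge questions.* A reader might infer this from the list, but the protocol does not say the list is the order of administration.
- *The letter, leaflet and picture sheet tell controls the facts.* The attachments are only listed. Their text, and whether controls receive the picture sheet, are not established. The described questions alone show that the mailing discloses the topic.
- *The wrong item is used.* Not shown. A storage and research item may be in the knowledge block. What stands is that none is named or anchored.
- *The item invites prompting.* It is already in the past tense, which limits prompting but does not remove it, since it does not separate knowledge before the mailing from knowledge gained through it.
- *All arm contrasts shrink.* They need not. Opt-out plus versus opt-out has no planned consent difference to lose and could acquire one. Late informed consent returns may be refusals. The plan of analysis also does not list informed consent versus opt-out, although the sample-size section, Hypothesis 4 and the decision rule all bear on it.
- *Full-sample power is hardly touched.* Largely true, as the working shows. The stronger grounds are bias and decision rules without a margin.
- *A consent cut-off can go in the statistical analysis plan.* It can, provided the dates of forms and oral opt-outs are recorded. The wording, anchoring and placement of a questionnaire item cannot be repaired at that stage.

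**Conclusion.** The point holds in limited form. As written, primary outcome 2 would come either from an item on a different matter or from unspecified knowledge questions not tied to the time before the mailing. The mailing discloses the subject to controls, so a narrower active-versus-control awareness difference is the likely direction. Its size is unknown, and the full-sample test would usually keep its power unless the true gap is small. The open consent status could narrow informed consent versus the opt-out arms. It could also create a spurious difference between opt-out plus and opt-out. The 5.4-point and 2.9-point illustrations rest on assumed shares and are not forecasts. The change should be made, with medium confidence, because it is cheap before data collection and the awareness part cannot be corrected afterwards.

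**What to change.** **First-questionnaire section.** Name an item matched to primary outcome 2 and state that it opens questionnaire 1. Possible wording: before you received this mailing, did you know that removed tissue is stored, and did you know that it may be used for research? Keep the influence item as a secondary measure.

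**Intervention section or plan of analysis.** Take consent status for the primary comparison as it stands on the day before questionnaire 1 is mailed, on the same clock in every arm. The six weeks now run from different events in active and control patients, so one common starting event is needed. Record the date of each form and each oral opt-out, and report later changes separately as a sensitivity analysis.

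**Cost.** One added item, its placement, and a sentence or two on the cut-off. The planned pilot already allows minor questionnaire changes. The real downside is that valid forms arriving after the cut-off do not count in the primary rate. That slightly lowers the informed consent rate and leans towards the protocol's own hypothesis on consent rates, so the sensitivity analysis that counts them should appear beside the primary result.

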### **Data collection: interview**

The semi-structured telephone interview schedule broadly covers the same topics as the questionnaire, but in more depth.

### **Data collection: second questionnaire (see attachment C)**

The second questionnaire consists of:

- Questions to assess whether patients are aware of the fact that they could have had an influence on residual tissue use and if so, whether they still remember which decision they made, and whether they are still satisfied with this decision.
- Questions to assess how it would be for patients to be asked consent for a research protocol or to receive information on an unexpected finding some time after surgery.

### **Data collection: questionnaires for the medical staff**

The opinions of the medical staff (treating physicians and nurse practitioners) about the different consent procedures and the associated workload will be evaluated by a brief, structured questionnaire administered before and after the interventions.

The pre-intervention questionnaire (see attachment D) consists of:

- Questions about the current situation regarding asking consent for residual tissue use. These questions have been developed for this study.
- Questions to assess which consent procedure clinicians and nurses prefer and their views on the potential drawbacks and advantages (time pressure, properly informed patients) of each of the consent procedures. These questions have been developed for this study.

The post-intervention questionnaire (see attachment E) consists of:

- Questions about how members of the medical staff experienced the three consent procedures with respect to e.g. time pressure and administrative loads. These questions have been developed for this study.
- Questions about how consent procedures in which patients are actively informed about residual tissue use could best be implemented into clinical practice (e.g. timing of the information and who would be able to inform patients). These questions have been developed for this study.

All questionnaires in this study will be tested in a small pilot study. Minor modifications may be implemented based on the results of these studies.

### ***Sample size, statistical power***

Sample size is based on an expected response of 75%, allowing sufficient power to address the major outcomes, i.e. consent rates and preferences for procedures, in different subgroups of e.g. hospitals, age and gender. In order to test the hypothesis that the two interventions result in a difference of at least 10% in consent rates, 0.1% non-consent in the opt-out plus or opt-out group versus 10% in the informed consent group, 121 patients per group are needed (80% power and a 2-sided alpha of 0.05; with continuity correction). The difference of 10% is based on our earlier research and the difference is considered a relevant loss of patient materials for research which may lead to selection bias. Because the setting of diagnosis and treatment is different between surgical and outpatient settings and also between general and academic hospitals, it is important to be able to compare the responses in these subgroups. We have also shown in our earlier studies that educational level is associated with preference for a certain procedure and this may also drive response rates of patients. Therefore we propose to include in each intervention group up to 600 patients to be able to conduct subgroup analysis and include adjustment factors; with a response rate of 75% and hence with 450 participants per group we could stratify for 3 to 4 factors, i.e. 90-150 per subgroup, and still have enough power to investigate a difference in response rate of 0.1% versus 10%. Patients will not be stratified by education or sex; we expect these two factors to be equally distributed across groups.

Another reason to obtain a large sample size is that the percentage of non-consenters is small, while it is important to assess their opinions and reasons for non-consent. In the earlier intervention study, 4.6% of respondents indicated in the questionnaire that they wanted to withhold consent or that they did not know whether they wanted to. A sample size of 1800 patients and a response rate of 75% will lead to approximately 62 patients who want to withhold consent or are not sure which choice to make.

A sample size of 450 (based on a conservative estimate of a response rate of 75%) will suffice to test the hypothesis that patients prefer the opt-out plus procedure over the informed consent procedure by a difference of at least 10%, based on the difference found in our earlier studies, i.e. 43% versus 34% (75% power and a 2-sided alpha; with continuity correction). In addition, the sample size will be sufficient to test the hypothesis that patients in the opt-out plus procedure are more satisfied with the procedure they are subjected to than patients in the informed consent procedure. In our earlier research 82% of the patients in the informed consent procedure compared with 65% in opt-out plus procedure indicated that they were satisfied with the procedure.

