## ***Basic plan of analysis***

Analysis will first be performed to evaluate the comparability of the intervention groups and the control group at study entry in terms of sociodemographic and clinical characteristics. Student's t-test or appropriate non-parametric statistics will be used, depending on the level of measurement. If the groups are found not to be comparable on one or more background variables, those variables will be employed routinely as covariates in subsequent analyses using multivariate models, such as logistic regression.

The proportion of the outcomes in each intervention arm, i.e. consent rates and patients' satisfaction with and preference for a consent procedure, the proportion of patients aware of storage of tissue and research use, and the satisfaction with and preference for a consent procedure of the medical staff, will be evaluated by comparison of the informed consent

versus the opt-out plus group, and the opt-out plus versus the opt-out group by non-parametric or parametric tests as appropriate. Patient characteristics, satisfaction with and preferences for the information and consent procedures will be evaluated according to patient characteristics such as age, educational level, sex, hospital type, type of clinical procedure, and disease type. All analyses will be performed using SPSS.

A qualitative analysis of the information needs and appreciation of the patients for the consent procedures will be evaluated through questions in the questionnaire and telephone interviews with a representative group of patients who completed the questionnaire.

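### The protocol claims sufficient power for procedure preference within subgroups, but supports it only for consent rates; on its own preference figures the power falls short for all but the coarsest pooled splits

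*Protocol*

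**What the plan says.** All the power statements are in the protocol section 'Sample size, statistical power'.

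- The opening sentence says that the expected 75% response is "allowing sufficient power to address the major outcomes, i.e. consent rates and preferences for procedures, in different subgroups of e.g. hospitals, age and gender". It gives no subgroup size and no power figure.
- Later in the same paragraph, subgroup analysis is given as a reason for recruiting up to 600 per arm: "with 450 participants per group we could stratify for 3 to 4 factors, i.e. 90-150 per subgroup". That sentence ends by tying these sizes to a contrast of 0.1% versus 10%, which is the consent-rate contrast. Nothing comparable is offered for preference.
- The last paragraph of the section gives the preference calculation. A sample of 450 is said to be enough for opt-out plus against informed consent at "43% versus 34% (75% power and a 2-sided alpha; with continuity correction". No value of alpha is printed there. For consent rates the section does print one: "80% power and a 2-sided alpha of 0.05; with continuity correction".

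'Basic plan of analysis' compares informed consent with opt-out plus, and opt-out plus with opt-out, for the listed outcomes, including preference. It adds that "satisfaction with and preferences for the information and consent procedures will be evaluated according to patient characteristics such as age, educational level, sex", with hospital type, clinical procedure and disease type also named. 'Study objectives' lists differences in preference by such characteristics among the additional questions.

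**The concern.** The opening sentence gives preference the same assurance of subgroup power as consent rates, but the argument that follows covers consent rates alone. The two contrasts differ greatly in difficulty. With 0.1% in one group, that group contributes almost no variance, and the gap is about 10 points. With 43% and 34%, both groups have nearly the largest variance a proportion can have, and the gap is 9 points. If 450 gives 75% power for preference, a subgroup of a fifth to a third of that size cannot have sufficient power for the same difference with the same test.

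What is at stake is how subgroup results are read, together with part of the case for the sample size. A reader told that subgroups were adequately powered for preference may take a non-significant difference in one hospital type, age band or diagnosis as evidence that patients there have no preference. They may then conclude that the best procedure differs between settings. Preference is also one of the criteria that the 'Outcomes' section uses to identify the best procedure for patients.

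**Working it through.** **Inputs**

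- Preference proportions 43% and 34%: sample-size section, last paragraph.
- Respondents per arm 450, from 600 × 0.75: "with a response rate of 75% and hence with 450 participants per group". Total 3 × 450 = 1350.
- Subgroup size 90–150. It stands in a sentence about 450 per group, so it is read as per arm. Pooled over three arms it is 270–450.
- Two-sided alpha 0.05: printed for consent rates, assumed for preference. A smaller alpha would lower every power below.
- Even two-way split (assumed): 450/2 = 225 per arm, 1350/2 = 675 pooled.

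**Between-arm formula (two independent groups, n per arm)**

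Power = Φ[(d − c − 1.96·s0)/s1], where
- d = 0.43 − 0.34 = 0.09, and c = 1/n with continuity correction or 0 without;
- s0 = √(2 × 0.385 × 0.615/n), with 0.385 the mean of the two proportions;
- s1 = √((0.43 × 0.57 + 0.34 × 0.66)/n).

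*Step 1: the plan's own figure.* At n = 450: s0 = 0.0324, s1 = 0.0323, d − c = 0.0878. The argument of Φ is 0.749, so power is 77.3% (79.3% without correction). For 75% power with correction, 427 per group are needed. The printed 75% is therefore slightly conservative, and the statement that 450 suffices for it holds.

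*Step 2: the same formula at subgroup sizes.* Example at n = 90: s0 = 0.0725, s1 = 0.0722, d − c = 0.0789. The argument is −0.876, so power is 19.0%.

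| n per arm | with correction | without | exact Fisher |
|---|---|---|---|
| 90 | 19.0% | 23.5% | 19.9% |
| 150 | 31.6% | 36.0% | 31.9% |
| 225 | 46.2% | 50.1% | 45.9% |
| 450 | 77.3% | 79.3% | 77.5% |

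**One choice per respondent, arms pooled**

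If each respondent names one preferred procedure and the shares are compared in a single sample of n:

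Power = Φ[(0.09 − 1.96·√(0.77/n)) / √((0.77 − 0.09²)/n)], with 0.77 = 0.43 + 0.34.

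| n pooled | corresponds to | power |
|---|---|---|
| 270 | 90 per arm | 39% |
| 450 | 150 per arm | 59% |
| 675 | even two-way split | 76% |

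Simulation gives 39.4% at 270 and 58.6% at 450.

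**Sensitivity to a full 10 points (44% versus 34%)**

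The text speaks of at least 10%, while its two figures differ by 9 points.
- Between arms, 90–150 per arm: 23–38% with correction, 28–43% without.
- Between arms, 225 per arm: 55–59%.
- Pooled: 46% at 270, 67% at 450, 84% at 675.

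**Contrast with consent rates**

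The between-arm formula at 0.1% versus 10% gives 77% at 90 and 96% at 150 with correction. The 90–150 argument is roughly sound for the outcome to which the protocol attaches it.

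**The case against.** Several points on the other side are fair, and they set the limits of the finding.

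- *The 90–150 figure is not a preference claim.* It belongs to the consent contrast. A reader might infer that the protocol promises adequate preference power at 90–150 per arm, but the text does not say so. The fault is a general sentence without support for one of its two outcomes.
- *Some named subgroups are larger.* Gender is a two-way split, and so is hospital type if that is what is meant by hospitals. The hypothesis on preference concerns what most patients prefer, which fits one choice per respondent. On that reading an even split reaches 76%, or 84% at a full 10 points, which meets the protocol's own 75%. This stands. It does not carry over to the four separate hospitals or to finer age bands, nor to the between-arm comparison in 'Basic plan of analysis', where an even two-way split gives 46–50%.
- *A reader might infer that most subgroup comparisons would miss the difference.* That holds for the between-arm test at 90–150 per arm and for 270 pooled. It fails at 450 pooled, where the test would succeed about 59% of the time.
- *A reader might infer that the two paragraphs contradict each other outright.* They do not. The first gives no power figure for preference, and the second does not address subgroups.
- *The planned subgroup question may be another one.* 'Study objectives' asks whether preference differs across characteristics, which need not mean a separate test of the two procedures inside each subgroup. The protocol gives no effect size for such differences, so this reading leaves the power claim equally unsupported.
- *The harm is conditional.* Nothing in the protocol says that a non-significant subgroup result will be read as no preference, and the preference criterion in 'Outcomes' is not a subgroup test. The risk comes from the label of sufficient power.

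**Conclusion.** The point holds as an unsupported power claim. The protocol asserts sufficient power for preference in subgroups and argues it only for consent rates. At its own 43% versus 34%, with two-sided alpha 0.05 assumed, the claim fails for every between-arm subgroup size examined, from 90 up to 225 per arm. It also fails for pooled subgroups of 270 to 450, the best of which is 16 points below the stated 75% (8 points below if the difference is a full 10 points). It is met only for pooled, roughly even two-way splits analysed as one choice per respondent.

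The whole-trial preference power is not affected, and the subgroup argument for consent rates is roughly sound. The correction is worth making because the claim is part of the stated reason for the sample size and would colour how subgroup results are read.

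**What to change.** 1. In the opening sentence of 'Sample size, statistical power', limit the subgroup power claim to consent rates by deleting the reference to preferences. Alternatively, keep preferences but restrict the claim to two-way splits pooled over all arms.
2. In the paragraph on preference, print the alpha and state the subgroup power: about 19–32% with continuity correction (24–36% without) for 90–150 per arm, 46–50% for 225 per arm, 39–59% for 270–450 respondents pooled over arms, and about 76% for 675 pooled.
3. State that preference results by subgroup are exploratory and reported as differences with 95% confidence intervals, and that a non-significant subgroup result is not read as absence of a preference.

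The cost is a few sentences and a less favourable stated power for subgroups. No extra patients or data are needed.
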